### Safety assessments

All adverse events (AEs) that occur after the screening visit (or as soon as the medical history of the patient has been examined) are documented. The period of observation ends with the last study visit. All patients who have AEs, whether considered associated with the use of the investigational medical products or not, are monitored for outcome determination. AEs are collected systematically based on patients’ answers to applicable questions by the investigator, but spontaneous reports are recorded as well if AE criteria apply. For analyses, AEs are centrally coded according to MedDRA. The Data Monitoring Committee (DMC) is composed of three independent experts, meets regularly to review all data relevant to safety, and provides the sponsor with recommendations regarding trial modification, continuation, or termination.

### Auditing

Audits are planned to be performed based on regular risk-based evaluation. Regulatory authorities and auditors authorized by the sponsor may request access to all source documents, the CRF, and other trial documentation. Investigators are contractually bound to enable direct access to these documents and to support audit activities.

### Protocol amendments

Decisions regarding protocol amendments will be taken by the study core team encompassing the coordinating investigator, trial coordinator, trial statistician, medical coordinator, and data management. Meetings for reviewing all available findings and information are scheduled every 2 weeks.

### Sample collection

The samples will be collected at the following time points: (i) at baseline, (ii) after salvage therapy, (iii) after consolidation therapy, (iv) after each cycle of consolidation therapy, (v) after each cycle of maintenance therapy, (vi) at the end of treatment, (vii) every 3 months during observational follow-up, and at end of study. Provided patients’ applicable informed consent is given, biological samples are stored to develop further knowledge and understanding of diagnostic, prognostic and predictive markers present in AML patients.

### Data collection and handling

All data required as per the study protocol, including clinical and laboratory data, are documented by the investigator or an authorized member of the study team in the medical record of the patient and in the eCRF. Access to the eCRF is password protected and an audit trail is in place. Any entries are tracked and locked to prevent further editing. The investigator at the clinical site is responsible for ensuring that all sections of the eCRF are completed correctly. Entries are checked for plausibility and consistency via eCRF-inherent edit checks and visually by the monitors where necessary. Implausibility and missing entries are queried and to be clarified with the responsible investigator. All relevant documents and data collected within the study will be archived for at least 10 years after termination of the study.

### Ancillary and post-trial care

For all patients in the prophylactic arm, treatment ends after the 12th cycle of maintenance therapy (EOT). For all patients randomized to the MRD-triggered arm, who did not cross-over in the prophylactic arm, treatment ends after the 2nd cycle of consolidation therapy (EOT). After EOT patients are routinely followed-up and treated as per the standard of care at the discretion of the treating physician. The period of observation (and the overall study) ends for all patients when the last patient being included and alive has been followed for at least 730 days (2 years) counted from this patient’s day 1 (EOS).

### Study monitoring

Study monitoring is done by the Heidelberg Clinical Studies Coordination Center (KKS). The first monitoring visit at each study center is scheduled to occur at the end of the second patient’s induction therapy. Further monitoring visits at each study site will depend on the (i) recruitment success of study participants, (ii) the monitor’s assessment of the trial site’s compliance with applicable stipulations (e.g., number and severity of protocol deviations or deficiencies detected during study visits), (iii) the deficiencies detected via Central Data Review, and (iv) the assessment of the coordinating team. The monitoring is carried out according to a monitoring manual giving comprehensive guidance on monitoring activities (Source Data Verification rules, corrective and preventive actions, documentation of protocol violations, escalation of findings, etc.).

### Ethical and legal aspects

All the procedures set out in the trial protocol are designed to ensure that all persons involved in the trial abide by Good Clinical Practice (GCP) and the ethical principles described in the current version of the Declaration of Helsinki. The trial is carried out in keeping with local legal and regulatory requirements. The Coordinating Investigator ensures that all trial personnel are adequately trained and maintains a list to whom he has delegated significant trial-related duties.

Before being admitted to the clinical trial, all patients must consent in writing to their participation after having understood the nature, scope, and possible consequences of the clinical trial. Patients are requested to consent to biobanking and to secondary use of their pseudonymized data for yet not determined further scientific analyses. The data obtained in the course of the trial are treated pursuant to the General Data Protection Regulation (EU-DSGVO, EU 2016/679) and the Data Protection Law of the Federal State (Landesdatenschutzgesetz), and the § 40 (2a) AMG. For protection of these data, organizational procedures are implemented to prevent the distribution of data to unauthorized persons.

All planned substantial changes to the study (protocol amendments) are to be submitted to the EC and the competent federal authority requesting their approval. Records of relevant communication with the EC and the regulatory authorities are kept by the coordinating investigator.

### Access to data and dissemination policy

After the publication of the complete trial, access to selected raw data is intended. This must be done in accordance with the European data protection act and informed consent given by the patients.

The results from this trial will be presented at national (e.g., annual meeting of the German Society of Hematology/Oncology); meetings of the Competence Net “Acute and Chronic Leukemias”; and international meetings (e.g., meetings of the European Leukemia-Net; annual congresses of the European Hematology Association, the American Society of Hematology and the American Society of Clinical Oncology). The full results will be published in high-impact peer-reviewed medical journals in accordance with ICMJE guidelines [30]. It is planned to make trial data available for re- and meta-analyses, after the trial is completed and results are published.

The sample size required for a fixed design, assuming CR/CRi/CRh rates of 0.55 for the enrolled patients and 0.30 for the historical controls, would be a minimum of 60 assuming a logistic regression is performed at one-sided significance level *α*=0.05, the aspired power is 0.8, and number of matching partners per intervention patient is at least 1. Using this sample size as a starting point for several simulation studies, it was assessed that the maximal enrolment of 80 patients generated a desirable power of the used adaptive design for most scenarios. The trial sample size is recalculated based on a conditional power argument in an interim analysis after enrolling 20 patients and will hence range between 20 and 80. The assumed CR/CRi/CRh rate of 0.3 for historical controls was estimated based on two large IPD meta-analyses datasets of r/r-AML patients (“historical control”) [6, 7], while the assumed CR/Cri/CRh rate of 0.55 for the patients treated quizartinib was determined to reflect a treatment effect that can be considered as clinically relevant. The sample size for the fixed design was calculated using the software PASS v16, while the simulations we used to evaluate the adaptive design were done using R v3 (http://r-project.org). Randomized patients who do not receive the IMP quizartinib will be replaced. All patients receiving at least one dose of the IMP quizartinib must not be replaced. Due to the underlying disease, loss to follow-up is expected to be negligible.

For the analysis of the primary endpoint, a logistic regression model will be applied to assess the odds ratio of CR/CRi/CRh rate after salvage therapy for patients receiving Q-HAM versus matched controls not receiving Q-HAM. The null hypothesis H0: OR≤1 is tested against its alternative H1: OR>1 at a one-sided significance level of *α*=0.05. The logistic regression analysis will be adjusted for age, high-risk cytogenetics (yes/no), and CR1 duration <18 months (yes/no/not applicable due to refractory disease). Due to the adaptive nature of the trial, two separate logistic models will be fitted for the two trial stages and be combined using the inverse normal function approach. Determination of *p*-values, point, and interval estimates will take the adaptive nature of the trial into account. Concerning the secondary endpoints: EFS, OS, and RFS endpoints will be analyzed using a Cox regression model and Kaplan-Meier plots, CIR, and CID will be analyzed according to Gray 1988 [33] and via cumulative incidence plots, and quality of life will be analyzed descriptively according to the corresponding guidelines and EORTC recommendations. Safety endpoints will be analyzed descriptively. Analyses of the primary and secondary endpoints will be based on the full analysis population (all randomized patients with treatment groups assigned in accordance with the randomization, regardless of the treatment actually received (intention to treat (ITT)). For patients with incomplete follow-up, time to last follow-up date will be used as the censoring time in the analysis of time-to-event data. Otherwise, no imputation of missing data will be conducted. For the biometricians, patient treatment shall remain blinded from the time of randomization until the final database lock. The interim analysis and sample size recalculation will be conducted by an independent biometrician who is not involved in the conduct of the trial. Statistical analysis will be performed using SAS v9.4 or higher [34].

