**Methods:**

In this multicenter, upfront randomized phase II trial, all patients receive quizartinib combined with HAM (cytarabine 3g/m^2^ bidaily day one to day three, mitoxantrone 10mg/m^2^ days two and three) during salvage therapy. Efficacy is assessed by comparison to historical controls based on the matched threshold crossing approach with achievement of CR, complete remission with incomplete hematologic recovery (CRi), or complete remission with partial recovery of peripheral blood counts (CRh) as primary endpoint. During consolidation therapy (chemotherapy and allogeneic hematopoietic cell transplantation), patients receive either prophylactic quizartinib therapy or measurable residual disease (MRD)-triggered preemptive continuation therapy with quizartinib according to up-front randomization.

The matched threshold crossing approach is a novel study-design to enhance the classic single-arm trial design by including matched historical controls from previous clinical studies. It overcomes common disadvantages of single-armed and small randomized studies, since the expected outcome of the observed study population can be adjusted based on the matched controls with a comparable distribution of known prognostic and predictive factors. Furthermore, balanced treatment groups lead to stable statistical models. However, one of the limitations of our study is the inability to adjust for unobserved or unknown confounders.

Addressing the primary endpoint, CR/CRi/CRh after salvage therapy, the maximal sample size of 80 patients is assessed generating a desirable power of the used adaptive design, assuming a logistic regression is performed at a one-sided significance level *α*=0.05, the aspired power is 0.8, and the number of matching partners per intervention patient is at least 1. After enrolling 20 patients, the trial sample size will be recalculated in an interim analysis based on a conditional power argument.

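### The fixed-design size of 60 does not follow from the inputs printed with it, which give 48 trial patients; an input is unstated or the figure is wrong, and the discrepancy is conservative.

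*Protocol article*

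**What the plan says.** The Protocol article, section Sample size calculation and statistics, gives a fixed-design calculation with these elements:

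- Response rates: "assuming CR/CRi/CRh rates of 0.55 for the enrolled patients and 0.30 for the historical controls".
- Test: logistic regression, "one-sided significance level *α*=0.05".
- Power: "the aspired power is 0.8".
- Controls: the "number of matching partners per intervention patient is at least 1".
- Result: the required size "would be a minimum of 60 assuming a logistic regression is performed at one-sided significance level" 0.05.

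The same section repeats the test level for the primary analysis: "The null hypothesis H0: OR≤1 is tested against its alternative H1: OR>1 at a one-sided significance level of" 0.05. It treats loss to follow-up as negligible and names PASS v16 as the software, without the procedure or options. It states no dropout inflation and no allowance for covariates in the calculation, although the planned model adjusts for age, high-risk cytogenetics and duration of first remission.

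The 60 is then carried forward: "Using this sample size as a starting point for several simulation studies", which led to a maximum of 80. The abstract (Methods) says that "the maximal sample size of 80 patients is assessed generating a desirable power of the used adaptive design".

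**The concern.** The article prints what looks like a full set of inputs next to a result, so a reader can check it, and the result is about a quarter larger than the inputs support (60/48 = 1.25). Either an input is missing or one of the printed values is not the one that was used.

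The fixed-design line is the only numerical justification of the trial size in the article. The adaptive design is described as having desirable power in most scenarios, with no simulated figure. If the line cannot be reproduced, a reader cannot tell what level and power the starting point of the simulations stood for.

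**Working it through.** **Inputs** (all from Sample size calculation and statistics): p1 = 0.55, p0 = 0.30, difference 0.25, odds ratio (0.55/0.45)/(0.30/0.70) = 2.85; one-sided alpha 0.05 (z = 1.645); power 0.8 (z = 0.842); one control per trial patient, which is the least favourable case allowed.

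**Trying to reproduce 60.** Two-proportion formula with pooled variance under the null, mean rate 0.425. At 1:1 it equals the Hsieh formula for logistic regression with one binary covariate.

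n per group = [1.645·√(2·0.425·0.575) + 0.842·√(0.55·0.45 + 0.30·0.70)]² / 0.25²
= [1.645·0.6991 + 0.842·0.6764]² / 0.0625
= (1.1499 + 0.5693)² / 0.0625 = 47.3, so **48**.

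The Hsieh total is 94.6, again 47.3 per group.

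**Other standard tests, same inputs:**

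| Test | Trial patients at 1:1 |
|---|---|
| Unpooled variance: 2.486²·0.4575/0.0625 = 45.3 | 46 |
| Pooled / Hsieh | 48 |
| Wald on log odds ratio: 2.486²·8.802/1.048² = 49.6 | 50 |
| McNemar, independent pairs: 49.3 | 50 |
| Continuity-corrected | 55 |
| Fisher exact, one-sided | 55 |

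None reaches 60. With more controls the pooled formula gives 36 trial patients at 1:2 and 31 at 1:3, so the allowance for more than one partner cannot explain a minimum of 60.

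**Power at 60 per group, one-sided 0.05.** Pooled formula: Φ[(0.25·√60 − 1.1499)/0.6764] = Φ(1.163) = 0.878. The Wald formula gives 0.862, exact enumeration of the unadjusted Wald test 0.882, and Fisher's exact test 0.853.

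**If 60 meant both groups together** (30 each): Φ[(0.25·√30 − 1.1499)/0.6764] = Φ(0.324) = 0.627. This is not the natural reading, because the section counts controls per trial patient and gives a trial size of 20 to 80.

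**What does lead to about 60:**

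- One-sided 0.025: (1.960·0.6991 + 0.5693)²/0.0625 = 60.2, so 61; power at exactly 60 is 0.799.
- One-sided 0.05 with a target power of 0.88: 61.
- One-sided 0.05, power 0.8, covariate R-squared 0.20: 47.3/(1 − 0.20) = 59.1, so 60. With the Wald formula, 60 corresponds to R-squared 1 − 49.6/60 = 0.17.

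Each requires a value that is not printed or that differs from the one printed.

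**The case against.** The best defence is the covariate allowance. The planned analysis is an adjusted logistic regression, and inflating the size for correlation between treatment and covariates belongs to that kind of calculation. A round R-squared of 0.20 gives exactly 60 at the printed level and power. Options entered in the software are often left to a full protocol, which is not shown. This stands as a possible explanation. It does not make the line correct as printed, because the article lists its assumptions and leaves this one out. Such an allowance also needs a reason here, since matching on these factors is meant to bring the correlation close to zero. It is not excluded either: the article says that the matching rate is not known in advance, so some residual imbalance could reasonably be planned for.

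Three stronger readings are tempting, and the document supports none of them.

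- **The calculation was really done at one-sided 0.025.** That gives 61 rather than 60, and the article gives one-sided 0.05 wherever it states the level. It is a candidate, not a finding, and it gives no ground for changing the test level.
- **The adaptive design's operating characteristics are therefore wrong.** The article prints no numerical ones. The maximum of 80 was judged by simulating the adaptive design itself, with 60 only as a starting value, and the second-stage size comes from a conditional-power recalculation after 20 patients.
- **An overstated requirement contributed to the trial's failure.** Trial status reports 11 patients at closure, short of the 20-patient interim analysis, and names slow recruitment and growing use of gilteritinib. Whether the figure was 48 or 60 made no difference.

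**Conclusion.** The point holds in a limited form. The printed inputs give 48 trial patients, or 46 to 55 depending on the test; the article prints 60. With 60 patients and 60 controls, power at one-sided 0.05 is about 88% rather than 80%. The cause cannot be settled from the article.

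The discrepancy is conservative: under the stated inputs, 60 overpowers a fixed design and leaves the type I error and the decision rule untouched. Its practical impact is modest. It matters because a stated figure on which later planning was built cannot be reproduced.

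The result assumes that 60 counts trial patients, that each has one control, and that treatment is uncorrelated with the covariates. Relaxing the second lowers the requirement. Relaxing the third raises it, and reaching 60 needs an R-squared of roughly 0.17 to 0.21 (1 − 47.3/60 = 0.21).

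**What to change.** Restate the fixed-design line so that size, level and power agree, in whichever of these forms matches what was done:

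1. 48 trial patients for 80% power at one-sided 0.05, with one control each; or
2. 60 trial patients with about 88% power at one-sided 0.05; or
3. 60 trial patients for 80% power at one-sided 0.05, with the covariate R-squared (about 0.2) stated and justified for a design that matches on those covariates.

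Name the PASS procedure and its options. Confirm which inputs fed the simulations behind the maximum of 80, and rerun them only if those inputs were wrong.

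The cost is a sentence or two and a check of the archived calculation, with at most a rerun of existing simulation code. No patients are needed, and neither the test nor its level has to change on this account.

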## Discussion

According to one clinical study, patients with *FLT3*-ITD mutated acute myeloid leukemia who relapsed less than 6 months after initial treatment have a dismal prognosis with median overall survival of fewer than four months [35]. Midostaurin plus chemotherapy showed to be efficacious in patients with newly diagnosed *FLT3* mutated AML [11]; however, midostaurin has negligible activity in patients with relapsed or refractory AML. Gilteritinib and quizartinib are possible therapy alternatives in *FLT3*-mutated r/r AML.

Gilteritinib is an oral FLT3/AXL inhibitor, which has been evaluated in a single-agent phase-I/II study [36]. The randomized clinical trial ADMIRAL randomized 371 patients with *FLT3* mutated AML refractory to one or two cycles of conventional anthracycline-containing induction therapy or with hematologic relapse after complete remission. Two hundred forty-seven patients were randomly assigned to gilteritinib single agent and 124 to salvage chemotherapy [37]. Overall (0.64; 95% confidence interval [CI], 0.49 to 0.83; *P*<0.001) and event-free survival (hazard ratio for treatment failure or death, 0.79; 95% CI, 0.58 to 1.09) were better in patients randomized to gilteritinib. Complete remission with full or partial hematologic recovery was achieved in 34.0% in the gilteritinib arm and in only 15.3% in the chemotherapy arm. In addition, a higher proportion of patients in the gilteritinib arm (63 patients, 25.5%) proceeded to allo-HCT compared to the chemotherapy arm (19 patients, 15.3%). However, despite all the beneficial effects of gilteritinib, survival after 24 months was not different between the chemotherapy and gilteritinib arm of the study and was below 20% in both arms.

Quizartinib was evaluated in a phase III randomized, controlled clinical trial (QuANTUM-R), which was conducted in patients with *FLT3-*ITD-positive AML with single-agent quizartinib. In contrast to the ADMIRAL trial, the QuANTUM-R trial included high-risk patients with a duration of first complete remission of ≤6 months and only AML with *FLT3*-ITD. In total, 367 patients were enrolled, of whom 245 were randomly allocated to quizartinib and 122 to chemotherapy alone. Overall survival was significantly longer for quizartinib compared to chemotherapy (hazard ratio (HR) 0·76 [95% CI 0·58-0·98; *p*=0·02]). Seventy-eight patients (32%) in the quizartinib arm and 14 patients (11%) in the chemotherapy arm proceeded to allo-HCT [38]. Complete remission with full or partial hematologic recovery was achieved in 48% in the quizartinib arm and in only 27% in the chemotherapy arm. Again, despite all beneficial effects of quizartinib, survival after 24 months was poor and not different between both therapy arms.

Thus, both studies showed dismal and similar outcomes beyond 24 months in both the *FLT3*-inhibitor and the chemotherapy arms. This was seen despite a much higher percentage of patients achieving a response and proceeding to an allo-HCT in the *FLT3*-inhibitor arms, indicating the development of secondary resistance.

Currently, there is no commonly accepted standard for salvage chemotherapy treatment [39]. Allogeneic hematopoietic cell transplantation offers the highest chance of cure in this clinical circumstance. Thus, the objective of the salvage therapy is to reduce leukemic burden, achieve the best possible remission, and perform a hemopoietic stem-cell transplantation [2]. However, a poor response to salvage therapy in patients with relapsed or refractory *FLT3*-ITD acute myeloid leukemia often prevents them from being bridged to hemopoietic stem-cell transplantation, and according to a previous publication, the best timing of allogeneic hematopoietic cell transplantation is after salvage chemotherapy if CR is achieved [6, 7]. This is further supported by data of an extended Cox regression model combining the time-dependent covariables response to salvage therapy (*P*<0.0001) and possibility to perform an allo-HCT (*P*<0.0001) [7, 40].

Several studies indicate a very low probability for achieving a second CR with standard intensive salvage therapy in patients exhibiting a *FLT3*-ITD, arguing in this clinical situation for experimental approaches [41, 42]. First studies concerning the combination of quizartinib with chemotherapy demonstrated that quizartinib is well tolerated and provided sufficient clinical benefit when administered as 40mg dose once daily [18]. Thus, the comparison of quizartinib with intensive salvage therapy versus chemotherapy alone appears as a logical consequence in terms of efficacy and safety.

We designed a randomized phase-II study to compare quizartinib as adjunct to intensive salvage therapy to salvage therapy alone in terms of CR/CRi/CRh achievement using a threshold crossing approach with matched historical controls based on individual participant data from available datasets [6, 7]. In an attempt to keep sample size on a manageable scale and overcome the common disadvantages of single-armed and small randomized studies, the presented matched-threshold crossing was designed to enhance this single-arm trial by including matched control patients with an equal distribution of known prognostic and predictive factors. Our approach combines matching of historical controls and adaptive sample size recalculation within a two-stage design. Furthermore, it allows us to evaluate the experimental treatment in all included patients, it is more cost-effective than a randomized clinical trial, and it enables us to adjust for known confounders. However, one of the limitations of our study is the inability to adjust for unobserved or unknown confounders.

One of the current challenges in AML treatment is finding effective and well-tolerated post-remission therapies to produce lasting or permanent remissions after achieving a CR since this could lead to a reduction in relapse that is known to be significantly high in this group of patients. Regarding the use and efficacy of maintenance therapy with *FLT3* inhibitors, a recent publication reported the results of the European Group for Blood and Marrow Transplantation (EBMT) registry-based study, which included 462 patients with *FLT3* mutated AML. Sixty-two patients received posttransplant sorafenib: 19 prophylactic, 9 as preemptive therapy, and 34 as a treatment for relapse [43]. The multivariate analysis showed that maintenance with sorafenib significantly improved relapse-free survival (HR= 0.44 [95% CI 0.26–0.75; *p*=0.001). A preplanned pair-matched analysis was performed on data from 26 patients in the sorafenib maintenance group and 26 controls. After a median follow-up of 39 months, the 2-year leukemia-free survival (LFS) and OS were 79% and 83% in the sorafenib group, and 54% and 62% in the control group (*p*=0.002 and 0.007, respectively) [42].

Thus, the second objective of this study is to compare in a randomized manner the efficacy of prophylactic quizartinib therapy to MRD-triggered preemptive continuation therapy with quizartinib in terms of event-free survival. To our knowledge, no study so far has evaluated prophylactic maintenance with quizartinib vs. MRD-triggered continuation quizartinib-therapy.

